### Research ethics

The Regional Ethical Board for Medical Research Ethics, committee South East B approved the study protocol in 2011 (#2011/1320). Any significant modifications to the protocol will be forwarded to the committee for approval.

The ethical obligation of the Helsinki Declaration to minimize harm to research participants, specifically the risk of overdose, has influenced two main design characteristics:To administrate medications openly (open-label) rather than use a masked, placebo-controlled design. While a placebo design increases internal validity and the precision of efficacy estimates, generalizability and estimates of clinical effectiveness may be reduced. In particular, a placebo design with this population risks ‘self-unmasking’ by use of illicit opioids [35] reducing the potential benefit of a masking procedure and increasing risk of illicit opioid use by participants, enhancing their vulnerability to overdose and relapse during or after study participation.Because transferring patients to standard treatment would either re-instate physical dependence on prescribed opioids like methadone in ART or risk relapse and overdose in medication-free abstinence, we consider the best solution to offer continuation of XR-NTX medication to participants post completion of the 12-Week phase as the alternative. This will also enable the collection of much needed long-term data on XR-NTX. BP-NLX patients who wish to continue on their medication will be offered to do so as part of the national ART program.

### Participants & setting

Patients have been recruited during the period from November 2012 to July 2015 by trained personnel based at five research hospitals in urban centers in Norway: Oslo University Hospital, Akershus University Hospital, Haukeland University Hospital, Stavanger University Hospital, and Vestfold Hospital Trust. An agreement is in place between the study management and the Directorate of Norwegian Correctional Service for study sites to recruit opioid users who are completing criminal sentencing in criminal justice facilities.

Opioid dependent (DSM-IV) adults (18+) without serious mental or somatic disease are eligible to participate: study personnel screen patients for acute or chronic suicidality or psychotic disorders using the MINI 6.0 interview [36], while a physician examines patients for serious somatic disease such as acute hepatic failure (Child-Pugh level 3+) or AIDS-indicator disease. Eligible patients can also be screened in an outpatient setting before entering detoxification in a protected environment (inpatient or closely monitored outpatient). All patients must be formally enrolled in Norway’s national ART program at one of the study sites in order to be eligible for randomization. This ensures personal follow-up by a counselor as part of standard outpatient treatment, and rapid access to other ART program resources (e.g. prescribed methadone) for patients who drop out of the study treatments. As the effects of XR-NTX on fetal development are not yet known, female participants are screened for pregnancy during inclusion and assisted in finding effective contraception for the duration of the study. Patients treated with opioid-based analgesics for chronic pain conditions will only be eligible if successfully transferred to a non-opioid replacement (e.g. benzodiazepines).

### Recruitment procedure

Participants are recruited via written information on brochures, webpages, and posters at site clinics, and via personal contact with their counselor or physician. After receiving verbal and written information about the study from study staff, patients are screened for inclusion/exclusion criteria and sign the written informed consent. The consent form is based on the template of the Regional Ethical Committee for Medical Research downloaded from http://helseforskning.etikkom.no/ikbViewer/Content/253516/TemplateClinicalTrial%20revised%2020120209.doc Separate consent forms will be utilized in the event that ancillary studies are started that are outside the scope of the present consent.

#### Pre-randomization tapering of opioid agonists

As naltrexone may induce withdrawal symptoms by displacing any opioid agonists at opioid receptor sites, they are assisted in tapering and detoxification in order to facilitate the transition with as low a risk as possible. Detoxification and induction on to study medication is conducted in a controlled environment, usually an on-site inpatient detoxification unit. Only patients unwilling or assessed as unable to undergo inpatient detoxification, an outpatient detoxification with daily staff contact can be arranged with daily or bi-daily urine drug screening.

Buprenorphine is the recommended medication for alleviating opioid withdrawal symptoms during detoxification in Norway, and is administered to all participants at the discretion of the on-site treating physician. A higher dose is typically administered to ART patients habituated to a daily buprenorphine dose (16 mg/buprenorphine is the standard target dose in ART) tapered for a standard 2 mg/day, while a lower dose (2–4 mg buprenorphine/day) is typically administered to illicit heroin users. Any regular methadone users are required to taper down and discontinue methadone for a minimum of 72 h before randomization. Once participants are stable in the 0–4 mg buprenorphine/day range, they are considered ready for random allocation (1:1) to either standard treatment with buprenorphine-naloxone (target dosage 16 mg/day, range 4–24 mg) or extended-release naltrexone (XR-NTX) 380 mg every 28 days, for the upcoming 12 weeks/84 days.

### Randomization

Allocation is conducted by non-study personnel on a per-patient basis using a permuted block algorithm accessible via a computer program with full-entry tracking. Participants are randomly allocated with a 1:1 ratio to either XR-NTX or BP-NLX independent of site, setting (clinic or criminal justice) or gender. When a study staff member contacts allocation staff for inclusion and randomization, inclusion criteria are verified before the patient is formally included into the database and allocated to one of the two medication groups. Group allocation is communicated openly to study staff via telephone, who are then free to communicate the results of the allocation procedure to patient and clinical staff in an open-label manner.

### Study medications

Before discharge from a controlled environment, buprenorphine-naloxone patients are inducted on to a flexible dose of BP-NLX: Range 4–24 mg/day of buprenorphine, target 16 mg/day, with a 1/4 naloxone component (range 1–6 mg; 4 mg in the target dose). The approach is based on Norway’s national ART guideline on buprenorphine pharmacotherapy for opioid dependence, which is based on an evaluation of the scientific literature. For the BP-NLX group, medication is provided courtesy of existing healthcare services for opioid users in Norway.

For patients allocated to receive extended-release naltrexone (XR-NTX), tapering is continued with a flexible, standard 2 mg/day regimen followed by a minimum of 72 h without opioid agonists in order to prevent inducing withdrawal symptoms. A naloxone challenge (0.2–0.4 mg) is administered prior to the first XR-NTX (380 mg) dose in order to confirm the absence of opioid agonist. Following induction onto either study drug (usually 3–7 days), patients are discharged from detoxification and are requested to attend regular ART program counseling and present weekly urine drug tests for the next 12 weeks. As XR-NTX is currently not available for purchase in Europe, study management requested the manufacturer to supply it free of charge for this study without additional funding and without conditions for manufacturer influence over study implementation, analysis or dissemination. The XR-NTX manufacturer (Alkermes, Inc) complied with this request.

After the completion of the 12-Week follow-up, participants are asked whether they wish to continue for the long-term observation phase of the study (48 Weeks total observation time).

BP-NLX patients who wish to continue on their medication will be free to do so as part of the national ART program, but conclude regular participation in the study. BP-NLX patients who wish to transfer to XR-NTX will undergo a washout period with detoxification and naloxone test similar to procedures described for the XR-NTX induction (above).

### Outpatient follow-up

Weekly urine drug tests (UDTs) are administered on site, at the local laboratory or at the GP’s office. A scratch card incentive is offered for each UDT (a maximum of 12) in order to increase UDT attendance. Every 4 weeks, participants have scheduled follow-up with data collection on all outcomes of interest (see Fig. 1). This coincides with re-administration of XR-NTX for patients allocated to this group and could coincide with one of four standard weekly counseling sessions offered in the on-site ART clinic. All 4-week assessments (except UDTs) are continued for patients who complete the 12-week RCT and elect to participate in the 36-week long-term observation phase. Adherence is monitored through self-report and can be verified by consulting each patient’s electronic journal on the site clinic, where each dose collected of either BP-NLX or XR-NTX is registered.

**Fig. 1 Fig1:**
[figure not shown]
SPIRIT Flowchart of Study Events for the study’Optimal Prevention of Overdose Deaths and Opioid Relapse Following Discharge: A Multi-Center RCT of Naltrexone versus Buprenorphine in Norway’

### Discontinuation

Discontinuation can occur on the participants’ request and will be considered by the investigator should the participant develop conditions contrary to inclusion criteria; e.g. acute or repeated psychotic episodes or suicide attempts, life-threatening or debilitating somatic conditions not compatible with participation (e.g. pharmacological incompatibility, preventing outpatient follow-up), assessed by a physician to have need for opioid-based analgesics with no feasible non-opioid replacements, pregnancy, or failure to adhere to study medication regimens. For BP-NLX this study adheres to clinical guidelines for ART where a flexible regimen is used to determine the dosage based on feedback on withdrawal and craving symptoms; a failure to attend BP-NLX administration for two consecutive days or more is considered non-adherence. For XR-NTX patients, adherence conditions are violated if re-dosing occurs more than 4 days past the standard 28-day re-dosing interval. In both groups, site investigators may make exceptions for credible force majeure scenarios. As overdose risk is known to increase upon discontinuation of addiction treatment, investigators have been asked to facilitate transfer to regular ART for patients who wish to discontinue either study treatment.

### Data management

Study personnel are trained to administer the structured Europ-ASI interview (see below) as well as the other instruments and CRFs used in the study. All data are entered into a GCP-compliant database with complete entry tracking and double entry/verification. Following completion of the study, data will be de-identified and stored for an additional 15 years accessible to the sponsor in compliance with Norwegian and European regulations. Due to the sensitivity of data and the protection of privacy of individual participants the dataset, there are no plans to make data available in a repository or public database.

#### Regulatory approvals, data–and safety monitoring

The Common Terminology Criteria for Adverse Events (CTCAE) version 4 is used to classify adverse events at follow-up. Any event requiring medical intervention is registered (CTCAE level 2 or above). Medication-related Severe Adverse Events (SAEs) and Sudden Unexpected Severe Adverse Reactions (SUSARS) are reported to the Norwegian Medicines Agency (European Medicines Agency) and to the study drug manufacturers (Alkermes, Inc. and Reckitt-Benckiser, Inc.) within two working days. No interim analyses are planned, but the Sponsor (the University of Oslo, Norway) as well as regulatory authorities may stop recruitment and further medication with study medication in the case of an emergency, e.g. an unusual accumulation of SAEs or SUSARs attributable to study medication.

As all participants are enrolled in a local ART clinic, ART services are assigned the legal responsibility for monitoring of everyday safety of the patient with the option of discontinuing patients from ART if necessary (and thus from study participation). In addition, a local data and safety monitoring committee consisting of site investigator, site coordinator, and a representative of the clinical monitoring service are responsible for assessing data quality and safety at each study site. National management consisting of LT, and NK, conducts additional supervision, provide training and guidance and assess compliance with the study protocol of all serious adverse events. As this is an investigator-initiated trial, there are no competing interests and the sponsor, the University of Oslo, Norway, is represented by the National PI (LT).

All relevant study personnel are trained in ICH-GCP and CTCAE event registration. All participants are insured against SAEs attributable to study drug (XR-NTX) occurring during or after participation via the Sponsor’s membership in the Norwegian Drug Liability Association.

The regional monitoring authorities at the Oslo University Hospital and at Haukeland University Hospital are utilized as GCP monitoring services for this study. Site monitoring will occur after the first patient at each site, after the initial *n* = 10 at each site, and yearly until last patient has completed or discontinued participation and final monitoring of *n* = 10 random client report files (CRFs) at each site. The Norwegian Medicines Agency may conduct audits of the trial at any time without notifying the sponsor or investigators.

#### Outcomes & instruments

Urine Drug Test (UDT) data will be analyzed in accordance with recent Cochrane specifications as either a) proportion of total number of UDTs without illicit opioids or b) number of UDTs negative for illicit opioids received from each patient in each group during the 12-week randomized period [37].

Retention in treatment is defined in two ways: Number of days (of maximum 84 days) receiving effective pharmacological treatment, and number of patients completing the study at Week 12.

At baseline and every 4 weeks, patients undergo a structured interview and a selection of patient-reported outcomes: The European version of the Addiction Severity Index (the Europ-ASI) [38, 39] comprises drug and alcohol use, physical and mental health, work, education, social relations, and criminal behavior. The Europ-ASI is used for the second main drug use outcome measure, the number of days of abstinence from illicit opioid use in the 28 days preceding each interview for a total (maximum) of 84 days. To increase accuracy of responses relative to the Europ-ASI standard, timeline follow-back is used: a technique of backtracking and questioning about use and abstinence to obtain as accurate an estimate as possible of total number of days’ use of a specific substance in the 28-day follow-up period [40].

In addition to the primary outcomes, we explore secondary outcomes of importance to recovery: Number of patients fulfilling MINI [36] (DSM-IV) criteria for dependence on illicit opioids (exempting the 12-month criterion). The Addiction Severity Index administered every 4th week also records information on the use/abuse of alcohol, amphetamines, cannabis, sedatives (e.g. benzodiazepines), as well as other illicit substances (e.g. LSD, MDMA, GHB), and poly-drug use; days of injecting drug use; any overdoses (non-lethal) and hospitalizations in somatic or psychiatric health care; workdays and days engaged in illegal activities; number of days with conflicts in close relations, days physical and mental illness.

Craving for heroin is assessed using a 0–10 Visual analogue scale (VAS) on two questions: ‘I need heroin’ where ‘0’ signifies ‘Strongly disagree’ and 10 ‘Strongly agree’; and ‘How much have you been bothered by thinking about opioids or their use in the past 4 weeks?’ with 0 indicating ‘not at all’ and 100 ‘constantly’.

Mental health is assessed using the 25-item Hopkins Symptom Checklist [41], life satisfaction using the Temporal Satisfaction With Life Scale ‘present’ items [42]. Treatment satisfaction was assessed using a visual analogue scales of 0–10 on the questions ‘How satisfied/dissatisfied are you with having had/not having received XR-NTX in the previous 4 weeks?’ and ‘To what extent would you recommend XR-NTX to a friend who was in the same situation you were in when entering this study?’. Based on previous studies [17, 43] the frequency and euphoria (‘high’) from any illicit opioid use was investigated using visual analogue scales on a qualitative description of any effects, the similarity of the experience to un-blocked drug euphoria (‘high’), what they would be willing to pay for a similar experience had they been in active drug use. In addition, motivation for abstinence using the SOCRATES-8 days [44], and pain assessment using the McGill Pain Questionnaire Short Form [45]. Norwegian language versions are used for all instruments.

Priority will be given to collection of primary outcomes for participants who are assessed to be unable (e.g. due to intoxication) to complete follow-up on one or more visits.

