#### Registry data follow-up

The informed consent and Regional Ethical Board approval permits collection of registry linkage data based on the participants’ unique Personal Identity Number given to every permanent resident or employee in Norway upon birth or first residential/employment visa. The PIN is necessary for personal identification to public authorities and to open a Norwegian bank account. The PIN is also used in many registries and makes it possible to link information on individuals across registries [46]. Ethical Board approval has been granted to collect registry data for the study period and up to 1 year before, during and after participation in order to: a) compare data and events occurrence within the group and compare with other groups of interest and b) obtain data on patients who discontinue XR-NTX treatment. Data from the following registries will be included: The Cause of Death Registry, the Norwegian Prescription Database (NorPD), the Police Registry, the Norwegian Prison Registry and the Norwegian Patient Registry (NPR).

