### Statistical analyses

Statistical analyses on the randomized part of the study will be conducted by a non-study statistician on a final RCT data set in which the two study medications is masked as ‘Rx A’ and ‘Rx B’; any obvious characteristics of the two comparison medications will also be censored before data are made available for analysis. For between- group comparisons and to control for the effect of baseline characteristics, we will use a General Linear Mixed Models (GLMM) approach containing factors for treatment group, sex, and sex-by- treatment interaction, and with age, duration of opioid dependence, and duration of last pre-study inpatient detoxification as covariates. For outcomes violating the normality assumption, a General Alinear Mixed Models (GAMM) approach will be used. Regular statistics (e.g. ANOVA, linear regression) may be utilized if the arguments for using GLMM or GAMM over legacy analysis types are considered to provide limited benefit. Retention will be assessed with Kaplan-Meier curves and a log-rank test. Adverse events will be compared using Fisher’s exact test. The primary endpoints are tested with a two-sided α = 0.05. Where relevant, *p* values will be adjusted for multiplicity using the Bonferroni-Holm method to preserve family-wise type 1 error at 0.05. Once the statistician concludes data analysis of the RCT phase, study management will be able to access the final dataset.

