#### Determination of sample size

In compliance with current recommendations for non-superiority trials [34], a minimum sample size has been estimated for two scenarios:

The superiority scenario assumes that XR-NTX participants will have opioid-negative samples on a mean of 7 out of the total 12 (7/12 or 0.58) samples, while participants receiving buprenorphine-naloxone will display a mean of 4 opioid-negative samples (4/12 or 0.33). With a 95 % significance level (*p* < 0.05) and a standard deviation of 3 in both medication groups, and power (beta) set to 90 %, a sample size of 17 patients/medication arm or *n* = 34 total is estimated to be sufficient for analysis. The estimated frequency of opioid use in each group is based on data from Norwegian patients receiving sustained release naltrexone [22] or on the frequency of illicit opioid use during buprenorphine maintenance in the Norwegian national ART program.

In the non-superiority scenario, using a beta of 90 %, we assume that both groups will retain 70 % of their participants at the end of Week 12 and set 20 % as the non-superiority margin; this yields a minimum sample size of *n* = 58 in each group/*n* = 116 total.

Based on the sample size calculations and the risk of dropout of a significant proportion of participants, we have set the recruitment target for *n* = 180 total, or *n* = 90 for each medication group. This will be facilitated by characteristics of design (few exclusion criteria, open-label allocation, outpatient data collection often coinciding with medication and counseling), prioritization of amount–and types of data collected. Information about the study will be distributed at clinical sites as well as outreach -, housing- and criminal justice facilities and the internet; these efforts are anticipated to attract the initial *n* = 30 patients whose presence in the larger community of opioid users will be sufficiently inform more potential participants to contact study staff for information.

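### In the randomized comparison, overdose and hospitalization rest on interviews with no described follow-up of leavers, and the planned registry linkage is not tied to it

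*Protocol article*

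**What the plan says.** **Source of the outcomes.** In the protocol article, Outcomes & instruments, the Addiction Severity Index interview given every fourth week records "any overdoses (non-lethal) and hospitalizations in somatic or psychiatric health care". Both are secondary outcomes, and fatal overdose lies outside the item.

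**Follow-up of leavers.** The Discontinuation section gives its reason for arranging transfer to regular agonist treatment: "As overdose risk is known to increase upon discontinuation of addiction treatment". It describes no further study assessment. Outpatient follow-up extends the 4-weekly assessments past Week 12 only for patients who complete the randomized phase and choose to go on.

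**Missing data.** Analysis sets carries forward the value from the last attended follow-up or, if there was none, the value from inclusion. Model-based imputation is an option.

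**Registries.** Registry data follow-up plans linkage that includes the Cause of Death Registry and the Norwegian Patient Registry, for the study period and up to one year before and after participation. One purpose is to compare events within the group and with other groups of interest. The other is to "obtain data on patients who discontinue XR-NTX treatment". Statistical analyses does not mention registry events.

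**Expected retention.** Determination of sample size states: "we assume that both groups will retain 70 % of their participants at the end of Week 12". It sets 20 percentage points "as the non-superiority margin".

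**The concern.** Overdose during treatment and after stopping it is a leading safety question here. The Background raises greater vulnerability after naltrexone is stopped, and the Discussion returns to it. A patient who leaves cannot report a later event at an interview that does not take place, nor one that fell between the last attended visit and leaving. Interview-based observation thus ends where the document itself says risk goes up.

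Equal loss in both arms would understate risk in both. Unequal loss would distort the comparison. Unequal loss is plausible because the Discontinuation section defines non-adherence differently by arm: two or more consecutive missed days for BP-NLX, and re-dosing more than 4 days past the 28-day interval for XR-NTX. The registries could close the gap, but the document does not connect them to the 12-week comparison, and its wording on leavers names one arm.

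**Working it through.** **Inputs from the document.** Retention is 70% per arm at Week 12, so 30% are not retained: 0.30 × 90 = 27 per arm, 54 of 180. Interviews fall every 28 days, on days 28, 56 and 84. The retention margin is 20 points. No event rates are given.

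**Assumptions.** Patients leave at a constant rate. One arm retains 70% and the other 50%, that is, 70% less the margin. The 84-day event risk on treatment is 5%. The event rate after leaving is m = 1, 3 or 5 times the on-treatment rate. An event is recorded only if the next scheduled interview is attended; otherwise the interval counts as no event.

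**Step 1: share of on-treatment risk recorded.** With S(t) = S(84)^(t/84), the recorded share is about the mean of S(28), S(56) and S(84).
- 70% arm: (0.888 + 0.788 + 0.700)/3 = 0.792
- 50% arm: (0.794 + 0.630 + 0.500)/3 = 0.641
- Recorded ratio: 0.641/0.792 = 0.81, whatever m is, because events after leaving are never recorded

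**Step 2: true risk.** The mean fraction of the 84 days spent on treatment is (1 − S)/(−ln S), which is 0.841 for 70% and 0.721 for 50%. Relative cumulative risk is 0.841 + 0.159m and 0.721 + 0.279m.
- m = 1: 1.000 and 1.000, ratio 1.00
- m = 3: 1.318 and 1.558, ratio 1.18
- m = 5: 1.636 and 2.116, ratio 1.29

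**Step 3: simulation of the same model, 2,000,000 patients per scenario.** This removes the small-risk approximation.

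| m | True risk, 70% arm | True risk, 50% arm | True ratio (50% vs 70% arm) | Recorded, 70% arm | Recorded, 50% arm | Recorded ratio | Patients with an event missed, 70% arm |
|---|---|---|---|---|---|---|---|
| 1 | 5.0% | 5.0% | 1.00 | 4.0% | 3.2% | 0.81 | 21% |
| 3 | 6.5% | 7.6% | 1.17 | 4.0% | 3.2% | 0.81 | 39% |
| 5 | 7.9% | 10.0% | 1.27 | 4.0% | 3.2% | 0.81 | 50% |

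An on-treatment risk of 10% gives nearly the same ratios. The missed shares come from unrounded risks.

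**Step 4: does the stated missing-data rule change this?** For a yes/no outcome per patient, carrying forward a follow-up value leaves the patient's status as it was: an event-free last interview stays event-free, and a reported event is already counted. For event counts, it repeats an old event. Only patients with no attended follow-up receive the inclusion value, which describes life before study treatment. Under constant leaving they are 1 − 0.888 = 11% of the 70% arm and 1 − 0.794 = 21% of the 50% arm. In no case does the rule show an event after the last attended visit.

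**The case against.** The case against is strong on several points.

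- **Registries are already planned.** A reader might infer that these events are sought only at attended visits. That is not so: the linkage covers deaths and patient-registry contacts, and the Discussion assigns overdose after stopping naltrexone to it. Medication-related serious events are also reported quickly. What remains is that the document does not bring registry events into the randomized comparison.
- **Nobody is declared event-free.** A reader might infer that leavers and deaths count as having no event. No passage says so. Fisher's test is assigned to adverse events only ("Adverse events will be compared using Fisher’s exact test"), and deaths are sought in the Cause of Death Registry. The non-lethal limit reflects what a self-report interview can record. Inclusion values may even add pre-study events and push the comparison the other way.
- **The size depends on assumptions.** The 30% is a sample-size assumption, equal in both arms. With equal retention and otherwise identical arms, interview scoring produces no difference between them. The 0.81 needs unequal retention, and 50% is the margin's edge, not an expectation. Where the true ratio is 1.00, no direction is reversed.
- **One-arm registry filling is not a stated analysis.** A reader might take the wording on XR-NTX leavers to mean that registry events would be added for that arm alone. No passage plans that, and the linkage is described for participants in general.
- **Detail may sit elsewhere.** A fuller protocol or SAP may settle denominators and registry use. But the article itself fixes the interview as the source, gives the imputation rule, and names one arm in the registry purpose for leavers.

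**Conclusion.** The point holds in limited form. For overdose and hospitalization in the 12-week comparison, the stated source cannot see events after a patient's last attended visit, and the stated imputation does not repair this. The missed events favour the arm that loses more patients. Under the assumed 50% versus 70% retention, with unattended intervals counted as no event, the recorded ratio is about 0.81 against a true 1.00 to 1.27. At m = 3 and m = 5 it lies on the wrong side of 1. At equal 70% retention the comparison is not tilted between otherwise identical arms, but 21% to 50% of patients with an event go unrecorded. These are illustrations, since the document gives no event rates. The document does not support saying that deaths go uncounted or that leavers are classed as event-free.

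**What to change.** For the randomized phase, define two outcomes from allocation to day 84 in all randomized patients of both arms: any overdose, fatal or non-fatal, and any hospitalization. Score them from the Norwegian Patient Registry and the Cause of Death Registry, with the interview as a supplement, and do not carry event counts forward.

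Exclude the index detoxification stay from hospitalization. Patients are normally allocated during that stay, and XR-NTX patients continue tapering followed by at least 72 hours without opioid agonists, so counting it would build in a difference between arms.

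Reword the second registry purpose so that it covers patients who discontinue either study treatment. First confirm that the existing consent and ethics approval extend to BP-NLX leavers; the article describes both as permitting linkage for participants.

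Dividing events by person-time under observation is not a substitute, because it still omits events after leaving.

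The cost is mainly wording plus that check. The analysis must wait for the registry extract, and overdoses that never reach health care will stay unseen in patients who have left.
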